## Abstract

**Background:**

Knee osteoarthritis (KOA) is a progressive degeneration of the knee joint that has the potential to impair the function of the lower extremity. Tuina, as an important component of traditional Chinese medicine (TCM), is a common treatment for KOA. However, the prevailing practice often limits the therapeutic focus to the knee joint, overlooking potential coexisting hip and ankle injuries. Thus, the therapeutic efficacy may not be optimal in these instances.

**Objective:**

This study aims to evaluate the clinical efficacy of Tuina therapy based on hip-knee-ankle synergy combined with conventional treatment in patients with KOA. It also seeks to explore the potential effects on the lower extremity kinematic chain and provide clinical practitioners with a potentially valuable therapeutic approach.

**Methods:**

This single-blind randomized controlled trial (RCT) will involve a total of 96 participants with KOA from 1 study center (including 2 branches). Participants will be randomly divided into a conventional treatment (control) group and a Tuina+conventional treatment (intervention) group in a 1:1 ratio. Participants in the control group will receive regular health education, self-administered acupressure, and functional exercise. This routine will be completed in 4 weeks, with a total of 5 sessions planned each week. Participants in the intervention group will receive 8 sessions of Tuina therapy based on hip-knee-ankle synergy (twice a week for 4 weeks), combined with conventional treatment. The primary outcome of this study will be improvement in WOMAC (Western Ontario and McMaster Universities Osteoarthritis Index) scores from baseline to 16 weeks. Among the secondary measures, the Key Symptoms and Signs/TCM Syndrome Classification Quantitative Evaluation of KOA and the 11-item Tampa Scale of Kinesiophobia (TSK-11) score will be evaluated from baseline to 16 weeks. The Functional Movement Screen (FMS), the Timed Up and Go (TUG) test, and the Weight Bearing Lunge Test (WBLT) scores will only be evaluated at baseline and 4 weeks.

**Results:**

The trial commenced in September 2024 and is expected to conclude in September 2025. As of April 2025, key preliminary steps have been successfully completed. Specifically, the ethical review and clinical trial registration have been finalized. Participant recruitment is proceeding well, with 69 individuals having been enrolled to date. Data collection is currently ongoing, and formal data analysis has not yet been initiated.

**Conclusions:**

This RCT aims to contribute to the growing evidence base supporting the necessity of kinetic chain–based integrative diagnosis and treatment, while also evaluating the feasibility of the study protocol and exploring the benefits of manipulative therapy.

**Trial Registration:**

International Traditional Medicine Clinical Trial Registry ITMCTR2024000293; https://tinyurl.com/4tsszfdu

**International Registered Report Identifier (IRRID):**

DERR1-10.2196/75547

## Introduction

Knee osteoarthritis (KOA) [1,2] is a common musculoskeletal problem worldwide, characterized by pain, stiffness, swelling, and limited joint function. According to radiographic confirmation [3], KOA is estimated to affect about 3.8% of the world’s population. The incidence of this condition increases with age, with prevalence exceeding 10% in individuals over the age of 60 years, especially women. Several lifestyle factors [4,5] are known to heighten the risk of developing KOA. These include increased body mass, specific occupational roles that involve repetitive knee stress, and a history of traumatic knee injuries.

Although many guidelines [6-8] recommend physical exercise to improve pain and function in patients with KOA, pain and a fear of exercise injury are also major barriers to adherence to exercise. Only a few patients can follow the guidelines. As an additional option, Tuina therapy has become one of the preferred treatment methods for many patients. However, it is crucial for many clinicians to recognize the integral role of hip and ankle synergistic joints in knee joint injuries. These synergistic injuries may occur simultaneously or sequentially with knee joint injury, and their diagnosis and treatment should not be overlooked [9].

Traditional Chinese medicine (TCM), with its long-standing history and unique theoretical system, has garnered increasing attention for its role in managing KOA. Recent advances in translational Chinese medicine have further illuminated the potential of TCM-based approaches in addressing KOA. A study has shown that acupotomy can effectively upregulate the expressions of adenosine monophosphate–activated protein kinase (AMPK), Unc-51-like autophagy-activating kinase 1 (ULK1), and Beclin1; downregulate the expression of mechanistic target of rapamycin (mTOR); promote autophagy; and alleviate joint degeneration [10]. This highlights the complex mechanisms through which TCM influences KOA pathogenesis and progression. A network pharmacology study demonstrated that paeoniflorin exerts potent anti-inflammatory effects on synovial inflammation in osteoarthritis (OA) [11]. These findings bridge TCM and modern pharmacological approaches, offering novel insights into the development of effective TCM-based therapies for KOA. Additionally, research on Tai Chi outlines its benefits in alleviating physical impairments in patients with KOA, including improvement in muscle strength function, proprioception, and sleep function and reduction in joint mechanical stress, pain, and inflammation [12]. These studies further corroborate the efficacy and feasibility of TCM interventions in KOA management.

TCM [13] is highly influenced by the concept of viewing things in classical Chinese philosophy. The concept of holism permeates all areas of TCM, including physiology, pathology, diagnosis, differentiation, and treatment of the syndrome. TCM believes that the human body is an organic whole, including the hips, knees, and ankles. Indeed, the concept of holism is an essential component of TCM and underlies the practice of Tuina therapy. Therefore, the principle of integrity should be implemented in the treatment of KOA, and comprehensive judgment and holistic treatment should be emphasized [14].

To explore the scientific model of the interaction between bones, muscles, and joints and their functional transformation rules during human movement, modern medicine has proposed the concept of the kinematic chain. The synergistic effect of the lower limb kinematic chain, consisting of hip, knee, and ankle joints, is of paramount importance in the process of human movement. Any abnormality in the lower limb’s kinematic chain can lead to joint pain, muscle weakness, poor posture, and other complications, which can negatively affect an individual’s exercise performance and overall quality of life [15,16]. Therefore, in the treatment of KOA, we should not only focus on the local knee but also consider the corresponding changes in the hip and ankle and implement a targeted therapeutic approach.

Therefore, we hypothesize that Tuina has the potential to ameliorate clinical symptoms of KOA by correcting abnormalities in the lower limb kinematic chain and restoring the mechanical equilibrium of the lower extremities. We plan to conduct a randomized controlled trial (RCT) to evaluate the clinical efficacy of Tuina therapy based on hip-knee-ankle synergy in the kinematic chain of lower extremities in patients with KOA and explore the potential effect of synergistic therapy.

## Methods

### Study Design

A single-center, single-blind RCT has been registered with the International Traditional Medicine Clinical Trial Registry (ITMCTR2024000293). The study center is Shuguang Hospital affiliated with the Shanghai University of Traditional Chinese Medicine, a large tertiary hospital with 2 distinct campuses located in different regions of Shanghai, each serving diverse patient populations. The flowchart in Figure 1 illustrates the process of the study.

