### Participants

All participants will be recruited from among patients with KOA visiting Shuguang Hospital affiliated with the Shanghai University of Traditional Chinese Medicine. Patients will first be enrolled based on their basic information, medical history, X-ray results, and WOMAC (Western Ontario and McMaster Universities Osteoarthritis Index) scores. Patients who are willing to participate in this trial and demonstrate an understanding of the objectives and methods of the study by providing signed informed consent will then be randomly assigned to 2 groups: a conventional treatment (control) group and a Tuina+conventional treatment (intervention) group.

At baseline, some information will be collected in order to account for potential confounding variables, including basic information (name, sex, age, height, weight, telephone number, profession). We will calculate the patients’ BMI using their height and weight. Physical activity levels will be assessed and recorded using a 3-tier classification (light, moderate, and vigorous). Additionally, we will document the types of comorbidities and medication use, including type, dosage, and frequency. These variables will be included in multivariate analyses to adjust for their potential confounding effects on pain perception and functional outcomes.

All participants will be evaluated 4 times: at baseline and at 4-, 8-, and 16-week follow-up.

The inclusion criteria are as follows:

A diagnosis of KOA according to American College of Rheumatology criteria [17]Average pain score in WOMAC≥4An abnormal lower limb line on the lower limb length X-rayThe patient’s age is 20-65 years, male or female.No other treatment in the past 4 weeks that may interfere with the results of this study

In addition, patients with unilateral KOA will be included in the study.

The exclusion criteria are as follows:

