### Randomization, Allocation, and Blinding

Randomization will be performed using IBM SPSS Statistics 27.0 and manual assistance. Prior to the study, a randomization specialist will be assigned to generate a random set of numbers based on numbers 1-96 using IBM SPSS Statistics 27.0. After the numbers are sorted from small to large, the 96 cases will be randomly divided into the intervention group and the control group, and the numbers and corresponding groups will be sent to the researchers. Recruited patients who meet the inclusion criteria will be listed in a table and numbered in order of enrollment. The current caseload will be determined according to the grouping generated by randomly assigned personnel. The lists of the 2 groups will be sorted into tables and sent to the actual operators, who will be informed of the specific methods of operation of each group. This method can reduce unnecessary communication between researchers and randomization specialists in the grouping process as far as possible in order to reduce potential bias from researchers’ subjective intentions in participant grouping.

We have established rigorous assessment protocols and guidelines. An independent assessor, blinded to participants’ group allocations and unaware of the intervention methods used for the 2 groups, will conduct all outcome evaluations. Upon completion of the study, the assessor will be requested to estimate participants’ group assignments. Subsequently, their estimations will be compared with the actual group allocations. This procedure aims to evaluate the effectiveness of the blinding process. Should any breach of blinding be identified, we will thoroughly account for it and provide a comprehensive explanation within the data analysis and interpretation of results.

Information about the existence of another intervention group will not be disclosed to the participants, and they will be strictly instructed not to disclose any information related to their intervention to the assessor.

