We anticipate that the results of this study will demonstrate the effectiveness of Tuina therapy based on hip-knee-ankle synergy in improving pain relief, functional outcomes, and overall quality of life for patients with KOA. For example, we expect to observe statistically significant improvements in WOMAC scores, indicating reduced pain, stiffness, and functional limitations. We also expect to observe statistically significant improvements in TSK-11 scores, indicating reduced fear of movement in patients. Additionally, we expect to observe statistically significant improvements in TUG, FMS, and WBLT outcomes. Such improvements would suggest potential enhancements in patients’ physical activity and balance abilities. These potential findings would provide strong evidence supporting the integration of Tuina therapy into conventional treatment approaches for KOA, emphasizing the importance of considering the entire musculoskeletal system rather than focusing solely on localized treatments.

Although the study design inherently creates a potential imbalance in treatment dosage between the 2 groups, which may lead to differences in compliance and potentially affect the comparability of the results, several measures have been implemented to minimize the bias introduced by this imbalance. The assessor will be blinded to participants’ group allocations and remain unaware of the intervention methods used for the 2 groups. Additionally, information about the existence of another intervention group will not be disclosed to the patients, and they will be strictly instructed not to disclose any information related to their intervention to the assessor.

Our study was conducted in a single medical institution, a large tertiary hospital with 2 campuses in different regions of Shanghai that serve diverse patient populations. Although this setup partially mitigates the limitations of a single-center study, it does not fully replicate the diversity of multisite studies conducted across varied geographical areas. Future research should investigate the intervention’s effectiveness in multiple health care settings and populations to better understand its generalizability and real-world applicability.

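### Campus is left out of the stated adjustment variables although the trial recruits at two campuses from one unstratified list: a small, avoidable loss of precision, not a bias

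*Protocol article*

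**What the plan says.** The abstract describes "96 participants with KOA from 1 study center (including 2 branches"), and the Study Design section calls the centre "a large tertiary hospital with 2 distinct campuses located in different regions of Shanghai, each serving diverse patient populations".

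The Randomization, Allocation, and Blinding section has a specialist "generate a random set of numbers based on numbers 1-96 using IBM SPSS Statistics 27.0", after which "the 96 cases will be randomly divided into the intervention group and the control group". Patients take their place on the list by enrolment: "Recruited patients who meet the inclusion criteria will be listed in a table and numbered in order of enrollment". No stratum is named, so this is one pool and one sequence across both campuses.

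The Participants section says that "some information will be collected in order to account for potential confounding variables, including basic information". It lists sex, age, height, weight, profession, BMI, physical activity level, comorbidities and medication, and states: "These variables will be included in multivariate analyses to adjust for their potential confounding effects on pain perception and functional outcomes". Campus is not on the list. The Statistical Analysis section plans linear mixed effects models over the four visits, and covariance analysis where a baseline characteristic needs adjustment. It names no campus term.

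The Strengths and Limitations section returns to the two campuses and their patients: "Although this setup partially mitigates the limitations of a single-center study". It then concedes that the setup falls short of a true multisite study.

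**The concern.** The article treats the campuses as a noteworthy feature of the design and cites their patient diversity in support of generalisability. Yet campus enters neither the allocation nor the stated covariate list. Where a patient is treated can carry differences in case mix, staff and teaching that the listed variables capture only in part.

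With one list for both campuses, the arms are balanced in total but not within campus. If campus predicts the outcome, two things follow. The arms can differ in campus share by chance, which moves the estimate in that particular trial. And the variation due to campus stays in the residual, which widens the confidence interval. Both are avoidable with information that is known for every patient.

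**Working it through.** **Inputs from the article.** Sample Size Calculation: two-sided alpha 0.05, beta 0.1, SD 44.7, mean difference 32.6, 20% dropout. Abstract: 96 patients, 1:1, so 48 per arm.

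**Inputs assumed, because the article gives none.** Campus share of enrolment: 50%, 30% or 20%. Difference in WOMAC between campuses: D = 10, 20 or 30 points. Completers: 40 per arm.

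**Step 1: the article's own figure.** n = 2 × [SD × (z₀.₉₇₅ + z₀.₉₀) / difference]² = 2 × [44.7 × (1.96 + 1.28) / 32.6]² = 39.47 per arm. This matches the stated figure, so SD 44.7 and difference 32.6 are the right yardsticks. The unadjusted standard error with 40 completers per arm is 44.7 × √(2/40) = 10.0 points.

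**Step 2: how far campus share can drift between arms.** With 48 of 96 patients at one campus and 48 allocated to Tuina, the number given Tuina at that campus is hypergeometric with variance 48 × 0.5 × 0.5 × 48/95 = 6.06, so SD 2.46. The between-arm difference in campus share has SD 2 × 2.46/48 = 10.3 percentage points.

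| Share at one campus | P(imbalance ≥ 10 points) | P(imbalance ≥ 20 points) |
|---|---|---|
| 50% | 0.31 | 0.07 |
| 30% | 0.37 | 0.03 |
| 20% | 0.31 | 0.01 |

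Probabilities count both directions.

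**Step 3: shift in the estimate.** Shift = D × imbalance. The typical shift uses the SD of 10.3 points at a 50% share.

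| D | Typical (1 SD) shift | Shift at 20-point imbalance | As share of 32.6 |
|---|---|---|---|
| 10 | 1.0 | 2 | 6% |
| 20 | 2.1 | 4 | 12% |
| 30 | 3.1 | 6 | 18% |

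Even the largest of these is below the 10-point standard error. They also apply D to the score at follow-up. The abstract defines the primary outcome as improvement from baseline to 16 weeks. A campus difference that is the same at baseline and at follow-up cancels in that change, and only a difference in trajectory by campus remains.

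**Step 4: precision.** At a 50% share, campus explains D² × 0.25 / 44.7² of the variance:

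- D = 10: 25/1998 = 1.3%
- D = 20: 100/1998 = 5.0%
- D = 30: 225/1998 = 11.3%

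**Step 5: type I error and power by simulation.** 80 completers, 50% share, total SD held at 44.7, 5,000 runs per scenario, list left unstratified.

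| D | Power, no campus term | Power, campus as fixed effect |
|---|---|---|
| 0 | 89.4% | 89.0% |
| 10 | 89.2% | 89.4% |
| 20 | 89.2% | 90.5% |
| 30 | 89.5% | 92.0% |

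Type I error was about 4% to 6% in every scenario, with or without the campus term. The mean unadjusted estimate was 32.5 to 32.7 against a true 32.6. Stratifying the list as well as adjusting gave 90.4%, 91.0% and 92.6% for D = 10, 20 and 30, so most of the gain at the larger differences comes from the covariate.

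**The case against.** The strongest reply is that nothing is invalid here. Simple randomisation of 96 patients within one institution is an acceptable choice, and the standard error already allows for chance imbalance in factors outside the model. The simulation bears this out. A reader might infer that campus differences distort the arm comparison. The documents do not support that beyond the chance shift that any single allocation can bring.

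A reader might also infer that the two campuses have different patients. The article says that each serves diverse populations in different regions. It does not say that the campuses differ from each other on WOMAC, and it gives no figures. Part of any difference would be absorbed by the listed covariates, and the common Tuina operating procedure and uniform training should narrow differences in delivery. These points stand, and they are why the sizes above are a range under assumption.

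Third, a reader might fault the generalisability remark as untested. That remark is qualified, concerns breadth of recruitment and is followed by a call for work in other settings. By-campus estimates from 96 patients would be too imprecise to test it.

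Last, the statistical analysis plan, which is not shown, may already contain a campus term. What remains is narrower than simple silence: the article commits itself to a list of adjustment variables, and campus is not on it.

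**Conclusion.** The point holds as a minor, optional improvement. The single unstratified list and the omission of campus from the named adjustment variables are both in the text. The consequence is possible added noise and a small loss of precision. It is not bias and not an inflated type I error.

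Under assumed campus differences of 10 to 30 WOMAC points, a 20-point imbalance in campus share moves the estimate by 2 to 6 points. An imbalance that large has a probability of 1% to 7%, depending on how enrolment divides between campuses. The power gain from adjusting is about 0 to 3 percentage points. All of this rests on assumed shares and differences. The shift would be smaller to the extent that a stable difference in level cancels in change from baseline, and there is nothing to gain if campus is unrelated to outcome.

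It does not follow that the allocation list should be changed now. The article reports well over half of the 96 patients as already recruited (69 in the abstract, 55 in the Results section), and a covariate obtains most of what stratifying could give.

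**What to change.** Before analysis starts, add campus as a prespecified fixed effect to the adjustment variables in the Participants section and to the models in the Statistical Analysis section, for WOMAC and the secondary outcomes. Both places that report progress say that analysis has not begun, so this can still be done without knowledge of results. The Quality Assurance section says the protocol will not be altered during the study, so a dated entry in the statistical analysis plan is the natural place. If that plan already has the term, nothing more is needed.

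Optionally, report enrolment by arm and the treatment difference within each campus, descriptively and without tests.

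Leave the randomisation list unchanged.

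The cost is 1 degree of freedom and, if wanted, one table. If campus turns out to be unrelated to outcome, the loss is negligible: 89.4% against 89.0% power in the simulation with no campus difference.

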**Figure 1 figure1:**
[figure not shown]
Flowchart of the study. WOMAC, Western Ontario and McMaster Universities Arthritis Index; TSK-11, Tampa Scale of Kinesiophobia; FMS,: Functional Movement Screen; TSK-11: 11-item Tampa Scale of Kinesiophobia; TUG,: Timed Up and Go; WBLT,: Weight Bearing Lunge Test; WOMAC: Western Ontario and McMaster Universities Osteoarthritis Index.

### Participants

All participants will be recruited from among patients with KOA visiting Shuguang Hospital affiliated with the Shanghai University of Traditional Chinese Medicine. Patients will first be enrolled based on their basic information, medical history, X-ray results, and WOMAC (Western Ontario and McMaster Universities Osteoarthritis Index) scores. Patients who are willing to participate in this trial and demonstrate an understanding of the objectives and methods of the study by providing signed informed consent will then be randomly assigned to 2 groups: a conventional treatment (control) group and a Tuina+conventional treatment (intervention) group.

At baseline, some information will be collected in order to account for potential confounding variables, including basic information (name, sex, age, height, weight, telephone number, profession). We will calculate the patients’ BMI using their height and weight. Physical activity levels will be assessed and recorded using a 3-tier classification (light, moderate, and vigorous). Additionally, we will document the types of comorbidities and medication use, including type, dosage, and frequency. These variables will be included in multivariate analyses to adjust for their potential confounding effects on pain perception and functional outcomes.

All participants will be evaluated 4 times: at baseline and at 4-, 8-, and 16-week follow-up.

The inclusion criteria are as follows:

A diagnosis of KOA according to American College of Rheumatology criteria [17]Average pain score in WOMAC≥4An abnormal lower limb line on the lower limb length X-rayThe patient’s age is 20-65 years, male or female.No other treatment in the past 4 weeks that may interfere with the results of this study

In addition, patients with unilateral KOA will be included in the study.

The exclusion criteria are as follows:

Patients with severe bone and joint diseases, such as rheumatoid arthritis, osteoporosis, gout, or an active knee infection in the past 12 monthsPatients with cardiovascular, cerebrovascular, liver, kidney, hematopoietic, digestive, or mental illness or other conditions besides KOA that cause more restriction or pain in activities such as sitting, standing, or walkingPregnant and lactating women who cannot complete the radiological examinationPatients who cannot understand and complete research related to various scales and provide informed consentOther conditions that the investigator considers inappropriate to participate in the study

In addition, participants will be removed from the study under the following conditions:

Patients with severe adverse reactions or complicationsPatients who do not receive the treatment as initially intended or are prescribed therapy elsewhere without the investigator’s authorization

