### Cointervention Assessments

Patients will be advised not to receive other KOA interventions (eg, acupuncture, intraarticular injection) during the study. Additional interventions will be meticulously recorded.

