### Statistical Analysis

IBM SPSS Statistics 27.0 will be used for all data analyses. The different baseline characteristics of the 2 groups will be described. Data will be presented as the mean (SD) or the median (IQR) for continuous variables and as frequency distributions for categorical variables. The 2-sample *t* test for quantitative data or the chi-square test for qualitative data will be performed as a homogeneity test, and covariance analysis will be performed if an adjustment is needed for a baseline characteristic. Analysis will focus on whether statistically better treatment outcomes can be achieved in the intervention group. *P*<.05 is considered statistically significant and the tests are 2-sided. If data loss occurs, we will use multiple imputations to create several datasets to replace missing values and reduce bias. For repeated-measures data across 4 time points, we will apply linear mixed effects models to handle unequal intervals and account for individual random effects. In addition, repeated-measures ANOVA will test the statistical significance of variable differences between time points. Combining these methods will help reveal variable trends over time and provide reliable statistical support for the findings.

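### Randomised participants are removed from the study, not only from treatment, for events after allocation; this cuts off WOMAC follow-up to week 16 and can bias the comparison in either direction

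*Protocol article*

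**What the plan says.** After the exclusion criteria, the Participants section of the protocol article states that "participants will be removed from the study under the following conditions". One ground is a severe adverse reaction or complication. The other covers patients who "do not receive the treatment as initially intended or are prescribed therapy elsewhere", the outside therapy counting only where the investigator has not authorised it. The section does not separate stopping treatment from leaving the study.

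Five other places bear on this:

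- **Participants, visit schedule:** "All participants will be evaluated 4 times: at baseline and at 4-, 8-, and 16-week follow-up".
- **Abstract, Methods:** Tuina is given "twice a week for 4 weeks", while the primary outcome is the improvement in WOMAC "scores from baseline to 16 weeks".
- **Safety Assessments:** adverse events are recorded over the whole trial, including their duration and outcome.
- **Statistical Analysis:** for lost data, "we will use multiple imputations to create several datasets to replace missing values and reduce bias". Linear mixed effects models are planned for the outcomes measured at four time points.
- **Strengths and Limitations:** the unequal amount of treatment in the two arms could produce different compliance and affect comparability. The countermeasures listed are a blinded assessor and not telling participants about the other arm.

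**The concern.** Randomisation makes the arms comparable at allocation. A rule that takes people out because of what happens later, and because of how they tolerate or follow their assigned treatment, can undo that.

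The opportunities for removal are not the same in the two arms. Both follow the conventional routine five days a week, but only the intervention arm has eight therapist sessions to miss and manipulation to react to. Control participants, who get no Tuina, may be likelier to look for therapy elsewhere. The non-adherence ground has no stated threshold, and the outside-therapy ground turns on the investigator's authorisation. Under Randomization, Allocation, and Blinding, group lists go to the researchers and operators, so these decisions may be made with allocation known.

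At stake are the week 4, 8 and 16 WOMAC values of the removed participants. If they are never collected, no later definition of an analysis set can bring them back.

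**Working it through.** **1. What one removal costs.** Treatment ends at week 4 and the primary outcome runs to week 16. Removal before the week 4 visit loses three of the four WOMAC assessments (weeks 4, 8, 16). Removal between weeks 4 and 8 loses two, and between weeks 8 and 16 it loses the last. Each case contradicts the statement that all participants are evaluated four times.

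**2. The plan's own sample size.** Inputs from Sample Size Calculation: SD 44.7, difference 32.6, two-sided α 0.05, β 0.1, dropout 20%.

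- n = 2 × [44.7 × (1.96 + 1.28) / 32.6]² = 39.47 per group, as stated.
- 39.47 × 1.2 = 47.4, rounded up to 48, which matches the total of 96.
- Power at these inputs is 94.7% with 48 per group, and 89.2% with 48 × 0.8 = 38.4 per group.

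Precision is therefore not the issue. The dropout allowance covers lost numbers, not bias from who is lost.

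**3. Bias if removed participants are imputed.** Let p be the fraction removed in an arm and g the mean amount by which their true week 16 WOMAC exceeds (is worse than) the imputed value. The between-arm difference shifts by p(Tuina) × g(Tuina) − p(control) × g(control). With the same g in both arms this is (net excess removed) × g. The documents give neither p nor g. I assume g equal to the planned difference (32.6) or one SD (44.7).

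| Net excess removed | g = 32.6 | g = 44.7 |
|---|---|---|
| 10% | 0.10 × 32.6 = 3.3 | 0.10 × 44.7 = 4.5 |
| 20% | 0.20 × 32.6 = 6.5 | 0.20 × 44.7 = 8.9 |

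As shares of the planned 32.6, these are 10% and 14% in the first row, and 20% and 27% in the second. If the excess is in the Tuina arm and those removed do worse than imputed, the effect is overstated. If it is in the control arm, the effect is understated. If those removed do better than imputed, for instance because outside therapy helped, the sign flips again.

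**4. Bias if removed participants are simply excluded.** Assume no true effect, and removal from one arm only of the worst fraction r on a latent factor with correlation ρ to WOMAC. The shift is ρ × φ(z) / (1 − r) × 44.7, where z is the 1 − r normal quantile. For r = 10%, φ(z) = 0.1755, so ρ = 0.3 gives 0.3 × 0.1755 / 0.9 × 44.7 = 2.6 points.

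| r | ρ = 0.3: shift, type I error | ρ = 0.5: shift, type I error |
|---|---|---|
| 5% | 1.5 points, 5.3% | 2.4 points, 5.8% |
| 10% | 2.6 points, 5.9% | 4.4 points, 7.5% |
| 20% | 4.7 points, 7.7% | 7.8 points, 12.8% |

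The two-sided type I error is the same whichever arm loses people; only the direction of the false difference changes.

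**5. Whether the planned methods repair it.** Standard multiple imputation and the mixed model both rely on data being missing at random given what is modelled. Here the missingness is created by harm, non-adherence or outside care. Values borrowed from participants who stayed on their assigned treatment describe how the removed might have fared had they also stayed, not how they did fare.

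**The case against.** The strongest reply is that the removal wording concerns participation and defines no analysis set. An analysis plan that is not shown may well specify analysis by randomised group, so the lack of that statement here is no fault. Imputation and mixed models could also keep a removed participant's earlier visits in the allocated arm. This stands as far as it goes. It does not answer the point, which is a stated rule that stops data collection.

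Several stronger readings are tempting, and the documents do not support them:

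- **That the rule favours Tuina.** Removal for unauthorised outside therapy may fall more on controls, so the direction is open.
- **That only responders would be compared.** Lack of response is not a removal ground.
- **That harms are lost.** Safety Assessments has the triggering event recorded with its duration and outcome. Only observation after removal is unclear.
- **That removal contradicts Cointervention Assessments.** That section says "Additional interventions will be meticulously recorded", and removal applies only to therapy the investigator has not authorised. Recording every additional treatment and removing for some are compatible.
- **That missing any of the eight Tuina sessions triggers removal.** No session threshold is given.

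The magnitudes are also fairly challenged: a gap of the whole planned effect or a full SD is an assumption, and the exclusion calculation gives somewhat smaller shifts.

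**Conclusion.** The point holds in this form. The article removes randomised participants from the study for post-randomisation events tied to tolerance and adherence. Followed as written, this ends their WOMAC follow-up, conflicts with the four-visit schedule in the same section, and leaves later adverse-event follow-up unclear. The article itself accepts that compliance may differ by arm, and the blinding measures it lists do not touch removal.

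The bias can go either way and its size cannot be known from the documents. At a net 10% excess removal in one arm it would be 3.3 to 4.5 points with imputation, under the assumed gaps, or 2.6 to 4.4 points with exclusion, under the assumed correlations. These figures show scale only. A reader should not infer from them that a positive result would be spurious, or that any removal has yet occurred; the article reports none.

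It merits correction before analysis because the lost outcomes cannot be rebuilt afterwards.

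**What to change.** Reconcile the removal paragraph with the visit schedule in Participants and with Safety Assessments:

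1. Record the listed events as protocol deviations or treatment discontinuation, not as removal from the study.
2. Continue the week 4, 8 and 16 assessments and adverse-event follow-up unless the participant withdraws consent.
3. Make the primary analysis one of all randomised participants in their allocated group, whatever their adherence or outside therapy.
4. Use the present removal criteria only to define a per-protocol sensitivity set.
5. If anyone has already been removed, retrieve their remaining visits where possible.

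Quality Assurance says the protocol will not change during the study, so this needs a documented amendment, dated before analysis starts. The article reports recruitment still open and analysis not begun, so there was time for it. When treatment should stop is a clinical decision that this change does not address.

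The cost is a short amendment and some follow-up contacts on visits already scheduled. The stated sample size does not change. The treatment contrast may come out smaller, because people who left treatment or had other care are counted in their own arm.
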